While CBT-I is a first-line recommended behavioral intervention for insomnia according to guidelines from the American College of Physicians [25], the European Sleep Research Society [26], and the American Academy of Sleep Medicine [27], there are limited studies that have examined the effect of CBT-I on sleep outcomes and comorbid MS symptoms. We recently completed the first pilot randomized controlled trials to assess feasibility and preliminary efficacy of CBT-I modified specifically for pwMS [28,29]. Modifications that we made to the standard CBT-I program include: 1. For individuals who felt a nap was necessary for their health and wellbeing, the recommendation to avoid naps was modified to limit napping to ≤30 min, to take the nap as early in the day as possible, and delaying bedtime to a later time may be necessary until they were adequately tired; 2. For individuals with functional or mobility limitations or those who had concerns about falls (either individual or CBT-I provider), stimulus control was modified to perform a relaxation or distraction technique in bed; 3. For individuals who were concerned that the contraction portion of progressive muscle relaxation (PMR) might exacerbate spasticity (despite the standard instruction to gently tense muscle groups without causing discomfort), PMR was modified to focus solely on the relaxation component (i.e., releasing tension) without performing the contraction phase.

Whereas our pilot studies demonstrate feasibility and a large effect on sleep outcomes in pwMS following CBT-I [28,29], a well-designed adequately powered prospective randomized control trial (RCT) is needed to assess the efficacy of CBT-I delivered via telehealth compared to an appropriate control group to improve sleep outcomes (Aim 1) and fatigue and health-related quality of life (Aim 2). Also, determining the participant characteristics that predict improvement in sleep outcomes (Exploratory Aim 3) would help guide health care providers and individuals with MS to select an appropriate sleep intervention at an individual level.

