*Secondary Outcomes:* To explore the characteristics of participants that predict improvement in sleep outcomes (Exploratory Aim 3), disability (assessed by the Patient-Determined Disability Steps; PDDS) [32], depression (assessed by the Patient Health Questionnaire; PHQ-9) [41], anxiety (assessed by the Generalized Anxiety Disorder Assessment; GAD-7) [49], sleep self-efficacy (assessed by the Sleep Self-Efficacy Scale; SESS) [50], and adherence to the intervention are also assessed. Disability level, depression, anxiety, and sleep self-efficacy have a known bidirectional relationship with sleep and fatigue and are plausible predictors of responders and non-responders to CBT-I.1.Patient-Determined Disability Steps (PDDS) [32] scale is used to assess disability. It consists of a 9-point scale ranging from “normal” (score of 0) to “bedridden” (score of 8). The PDDS has been validated and highly associated with the Expanded Disability Status Scale [33].2.Patient Health Questionnaire (PHQ-9) [41] is a valid and reliable method to assess depression during the past 2 weeks. It consists of 9 items with a score ranging from 0 to 27. A tenth question that is not included in the summary score assesses how depressive symptoms affect functional level. The PHQ-9 is used as a screening tool and an outcome measure.3.Generalized Anxiety Disorder Assessment (GAD-7) [49] is a valid and reliable method to assess anxiety over the past 2 weeks. This questionnaire consists of 7 items, and the score from each item is summed for an overall score ranging from 0 to 21 with a higher score indicating a higher level of anxiety. An additional eighth question assesses if anxiety impacts daily activities and sociability.4.Sleep Self-Efficacy Scale (SESS) [50] is a 9-item self-report questionnaire used to measure sleep self-efficacy. The respondents indicate confidence in ability to accomplish 9 sleep behaviors on a 5-point Likert scale with 1 = “not confident” at all to 5 = “very confident”. The score ranges from 0 to 45 with a higher score indicating greater sleep self-efficacy.5.Adherence to CBT-I intervention: To assess adherence to the CBT-I intervention, the sleep log is used to assess number of mornings per week the participant got out of bed at agreed upon time, number of times got out of bed if unable to sleep within 20 min, and number of nights per week the participant conducted wind-down routine. A total percentage will be calculated and used as the outcome of interest.

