A ‘*Repeated Measures design’* with autocorrelation of ρ=0.5 (between the 6 week and 6 month assessment) and a type I error of 5 % was used to conduct the sample size calculations. With the assumptions mentioned above, for the *primary outcome of ISI*, a sample size of 17 in each of the two arms (n = 34 total) is required to detect a $\mu_{CBT-I}$ value of 13.8 versus $\mu_{Control}$ value of 8.1 (with common standard deviation σ=5.8) with 90 % power. Analogously, in the case of *primary outcome of PSQI*, a sample size of 25 in each of the two arms (n = 50 is required to detect a $\mu_{CBT-I}$ value of 6.7 versus $\mu_{Control}$ value of 4.6 (with common standard deviation σ=2.6) with 90 % power. Thus, max (34, 50) = 50 is chosen. The attrition rate from our prior preliminary efficacy trials of CBT-I in people with MS were: 16.7 % in-person CBT-I [28], 9.1 % in brief education [28], and 0 % in tele-health delivered CBT-I [29]. To be cautious, we will anticipate an attrition rate of 25 % due to the delayed reassessment, and so 50/0.75 ≈ 67 (rounded up to 68) is chosen. Looking at overall capability at enrolling participants, we have decided to enroll a total of 70 subjects in our study. We used the *‘Test for Two Means in a Repeated Measures Design’* platform in PASS 2020 to conduct our sample size calculations.

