#### Exploratory Aim 3: To explore the baseline characteristics of participants that predict improvement in sleep outcomes

3.2.3

HypothesisBaseline disability level, anxiety, depression, and sleep self-efficacy will predict responders and non-responders (i.e. higher disability, anxiety, and depression, lower sleep self-efficacy, and lower intervention adherence will predict non-responders; lower disability, anxiety, and depression, and higher sleep self-efficacy and level of intervention adherence will predict responders).

*Statistical Plan*: For Aim 3, the outcome is dichotomous (responders vs non-responders) and a logistic regression analysis will be conducted modeling responder status (defined as meeting the minimal clinically important difference of ≥ 6 points on the ISI) at 6 weeks. This will allow assessment of the effect of baseline predictors such as disability level, anxiety, depression, sleep self-efficacy level, and intervention adherence. The analysis will be conducted at the 5 % level of significance.

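### Exploratory Aim 3 treats on-treatment CBT-I adherence as a baseline predictor and dichotomises ISI change: keeping adherence confines the model to CBT-I, with about 3 expected non-responders, and pooling the arms still loses power

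*Protocol article*

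**What the plan says.** **The model.** Section 3.2.3 states that "a logistic regression analysis will be conducted modeling responder status", with response defined by a 6-point minimal clinically important difference on the ISI and evaluated at 6 weeks. It is meant to assess "baseline predictors such as disability level, anxiety, depression, sleep self-efficacy level, and intervention adherence". On testing it adds: "The analysis will be conducted at the 5 % level of significance". It names no analysis population, no arm term and no predictor-by-arm term. The section heading limits the aim to baseline characteristics.

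**Adherence.** Section 2.5 (item 5 of the Secondary Outcomes) and Table 2 derive adherence from the sleep log, as a percentage built from three behaviours: rising at the agreed time, leaving bed when sleep does not come, and keeping a wind-down routine. Both places describe it as adherence to CBT-I. Section 2.7.2 says that controls receive none of the active CBT-I components, and lists time in bed restriction and stimulus control among them.

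**Purpose.** Section 2.5 calls disability, depression, anxiety and sleep self-efficacy "plausible predictors of responders and non-responders to CBT-I". The Introduction expects Aim 3 to help providers and patients "select an appropriate sleep intervention at an individual level", and the Discussion repeats this.

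**Planning values.** Section 3.1 assumes, for ISI, a CBT-I "value of 13.8 versus" a control value of 8.1, with a common SD of 5.8. It describes these means as pilot change scores.

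**The concern.** A variable that accrues during six weeks of therapy is not a baseline characteristic, and one defined only by CBT-I behaviours has no value for a control participant. The predictor list therefore decides, without saying so, who can be analysed.

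The responder cut also sits far below the mean change assumed for CBT-I, so most participants fall on one side of it and the binary outcome carries little information.

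At stake is whether Aim 3 can deliver anything usable. One reading gives a model with almost no non-responders. The other gives a model of who improves in general, which differs from the stated use of choosing between interventions. The primary analysis is not affected.

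**Working it through.** **1. Confirm the planning values.** The plan gives no sample size, event count or power for Aim 3, so its ISI sample size serves as the check on the inputs. With two follow-ups correlated 0.5, the variance factor is (1 + 0.5)/2 = 0.75. Then n per arm = 2 × (1.960 + 1.282)² × 0.75 × 5.8² / (13.8 − 8.1)² = 2 × 10.51 × 25.23 / 32.49 = 16.3, rounded up to 17, as stated. The PSQI figure of 25 per arm reproduces in the same way. So 13.8, 8.1 and 5.8 are the plan's working values.

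**2. Responder share.** Assume normally distributed change at 6 weeks.
- CBT-I: Φ((13.8 − 6)/5.8) = Φ(1.345) = 0.911
- Control: Φ((8.1 − 6)/5.8) = Φ(0.362) = 0.641

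**3. Expected non-responders with 35 per arm.**
- CBT-I: 35 × 0.089 = 3.1. With SD 4 it is 0.9, and with SD 7 it is 4.6.
- Control: 35 × 0.359 = 12.6
- Pooled: 3.1 + 12.6 = 15.7 of 70

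In CBT-I alone this is 3.1/5 = 0.6 non-responders per listed predictor. The binomial chance of five or fewer non-responders is 0.91, and of none it is 0.04.

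**4. Simulated consequences.** Predictors are independent standard normals, with 35 per arm. For power, one predictor is correlated 0.4 with ISI change (an assumption). Logistic power is the two-sided 5% Wald test; linear power is the t-test on continuous change.

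| Model | Separation or no non-responder | Logistic power | Linear power |
|---|---|---|---|
| CBT-I only, five predictors together | about 28–34% | about 4% | about 64% |
| CBT-I only, one predictor | about 4–6% | about 16% | about 68% |
| Both arms, four predictors plus arm, no adherence | about 4% | about 61% | about 92% |

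A repeat run of 2,000 trials per cell, counting separated trials as non-detections, gave the same pattern. Its logistic power was 5%, 12% and 57% in the three rows, and its linear power 63%, 69% and 92%.

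**5. What each reading can answer.** In CBT-I alone there is no comparison arm, so predictors of response to CBT-I cannot be told apart from predictors of improvement under either programme. With both arms but no arm term, the planned gap in response (91% against 64%) is left unexplained and mixed with prognosis. With an arm term but no interaction, the main effects are prognostic only.

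**The case against.** **The model is not unworkable.** A reader might infer that the logistic model cannot work at all. The documents do not support that. Pooled without adherence, it is separated in only about 4% of trials and has fair power. In CBT-I alone it often converges, though to very imprecise estimates.

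**Two readings must be kept apart.** The count of about 3 non-responders belongs to a CBT-I-only model. The missing arm and interaction terms matter only if arms are pooled. Section 3.2.3 fixes neither, and reading them as joint defects of one model would be wrong.

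**Five simultaneous predictors is an assumption.** The text gives the predictors as examples and does not say that they enter together. One at a time, separation is rare, but power in CBT-I stays low.

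**Attrition.** A reader might reduce the arm to about 26 using the 25% in Section 3.1. That allowance is for the delayed reassessment, whereas Aim 3 is a 6-week outcome and the telehealth pilot lost nobody. The working therefore uses 35.

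**Prognosis may be the whole aim.** The heading speaks of predicting improvement, which main effects can address, and population or interaction terms could be set in an unseen analysis plan. This weakens the interaction point taken alone. It leaves untouched the mislabelled predictor, which stands in both the hypothesis and the model, and the cost of dichotomising. The exploratory label lowers the stakes but does not resolve the contradiction.

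**Conclusion.** The point stands in limited form. Calling adherence a baseline predictor contradicts the article's own definition, and keeping it restricts the fit to the CBT-I arm, with about 3 expected non-responders (0.9 to 4.6 for SD 4 to 7). Under either reading the binary outcome loses power against continuous ISI: about 4% against 64% in CBT-I with five predictors, and about 61% against 92% pooled with arm. Main effects alone do not support the use named in the Introduction and Discussion.

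These sizes rest on normal change scores, on 5.8 being the SD of change at 6 weeks, on means from a pilot with 10 per arm, on independent predictors and on an assumed correlation of 0.4. The linear figures are power for a main effect. A reader might carry them over to the interaction, but that is much harder to detect: about 38% power with 70 people if the correlation is 0.4 in CBT-I and zero in control.

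**What to change.** - Remove intervention adherence from the baseline predictor set, in the hypothesis as well as the model. Report it as a separate association within CBT-I.
- Model continuous 6-week ISI in all randomized participants, with baseline ISI, arm and one baseline predictor at a time (PDDS, PHQ-9, GAD-7, SESS).
- Report the predictor's main effect as prognostic and its interaction with arm as exploratory, each with a 95% confidence interval.
- Keep the responder rate at 6 points or more as a descriptive count by arm.

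The cost is a change of wording in the analysis plan, best made before unblinding; no new data or participants are needed. The drawback is that interaction estimates from 70 people will be imprecise, so they must stay labelled exploratory and cannot by themselves guide the choice of treatment.

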### Screening procedures

2.3

Potential participants undergo a standard phone screening process conducted by the study coordinator to determine eligibility.

Phone Screen:1.Standardized review of inclusion/exclusion criteria (Table 1).

**Table 1 tbl1:** Inclusion and exclusion criteria.

Inclusion Criteria	• 18–65 years old (upper age limit in place to reduce heterogeneity in sleep architecture changes due to aging) • Diagnosis of relapsing-remitting or secondary progressive MS based on established guidelines [56] and verified by their neurologist • Mild-to-moderately severe disability (≤6 on Patient Determined Disability Steps (PDDS) scale) [32] • Report of difficulty falling asleep, maintaining sleep, or waking up too early at least 3 nights/week for the past 3 months with significant distress and impact on function despite adequate opportunity for sleep and not due to other sleep disorders as indicated in the DSM-5 • ≥10 on Insomnia Severity Index [35] • English speaking • ≥ 31 on modified Telephone Interview of Cognitive Status [36] • Has a high school diploma or equivalent to serve as a proxy measurement of reading ability to ensure adequate reading ability to participate in the study • Report having access to internet service or a data plan and access to a computer, tablet, or smart phone

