Exclusion Criteria	• Known untreated sleep disorder (such as sleep apnea or restless legs syndrome) • >3 on STOP BANG indicating increased risk of sleep apnea [37] • Restless legs syndrome as determined by RLS-Diagnosis Index [39] • Circadian rhythm sleep-wake disorder as determined by the Sleep Disorders-Revised [40] • Parasomnia as determined by the Sleep Disorders-Revised [40] • Currently taking benzodiazepines, non-benzodiazepines, or melatonin supplements or agonists for insomnia • Score of ≥20 on the Patient Health Questionnaire (PHQ-9) indicating severe depression or endorsement of suicidal ideation (answer 1, 2 or 3 on #9 of the PHQ-9) [41] • Score of ≥15 on the Generalized Anxiety Disorder (GAD-7) indicating severe anxiety [42] • Current or history (up to 2 years) of alcohol or drug or alcohol abuse as indicated by DSM-5 criteria • History of other nervous system disorder such as stroke or Parkinson's disease • Currently pregnant or intending to become pregnant in the next 6 months. • Severe mental illness such as schizophrenia or bipolar disorder • Severe neurological or sensory impairments that would interfere significantly with testing • Relapse and/or corticosteroid use in the past 8 weeks • History of (within 5 years) or currently conducting overnight shift work including hours of midnight-4am • Currently receiving a behavioral sleep health intervention2.Disability will be assessed by the Patient-Determined Disability Steps (PDDS) [32] scale which is a single-item 9-point scale ranging from “normal” (score of 0) to “bedridden” (score of 8). The PDDS has been validated and highly associated with the Expanded Disability Status Scale [33]. A score of ≤6 is considered mild-to-moderately severe disability.3.The Insomnia Severity Index (ISI) [34] which is a valid and reliable measure of insomnia severity and consists of 7 questions each rated on a 0–4 scale. The range of scores on the ISI is 0–28, with ≥10 suggesting clinical insomnia [35].4.The 13-item modified Telephone Interview of Cognitive Status (TICS-M) [36] will be used to determine global cognitive status. A score 31 or greater will be considered non-demented [36].5.The 8 item STOP BANG [37] will be used to assess for risk of obstructive sleep apnea. A score of >3 is highly sensitive in detecting obstructive sleep apnea in various patient groups [38].6.The RLS-Diagnosis Index [39] will be used to screen for restless legs syndrome.7.The Structured Clinical interview for Sleep Disorders-Revised (SCISD-R) [40] will be used to screen for presence of circadian rhythm sleep-wake disorders and parasomnias.8.Depressive symptoms will be assessed using the 9-item Patient Health Questionnaire (PHQ-9), with a score of ≥20 suggesting severe depression [41].9.Anxiety symptoms will be assessed using the 7-item Generalized Anxiety Disorder (GAD-7), with a score of ≥15 indicating severe anxiety [42].

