#### Aim 1: To determine if CBT-I in individuals with MS will improve insomnia symptoms and sleep quality

3.2.1

*Hypotheses*: CBT-I will improve insomnia symptoms (primary outcome; measured using the Insomnia Severity Index) and sleep quality (measured using the Pittsburgh Sleep Quality Index) and will increase sleep efficiency and total sleep time (measured by actigraphy) compared to active control after intervention and after 6 months.

*Statistical Plan*: A repeated measures model (RMM) with two groups will be used to analyze the primary outcome of ISI and secondary outcome of PSQI at 6 weeks and 6 months. The analysis will be done adjusting for baseline as a covariate. With only two time points, the analysis is simplified (compound symmetry structure) and will be conducted using a type I error of 5 %. If there is a significant between group difference, we will use the pairwise comparison from the RMM to compare the two groups at 6-weeks and at 6 months. Point estimates of the mean scores for the two groups at all time points will be reported along with the corresponding 95 % confidence interval and p-values.

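### Exploratory Aim 3 does not name baseline ISI as a covariate, so the associations of its baseline predictors with response may be confounded by entry severity

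*Protocol article*

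**What the plan says.** - **Responder rule (section 3.2.3).** Response is dichotomous, "defined as meeting the minimal clinically important difference of ≥ 6 points on the ISI) at 6 weeks".
- **Predictors (section 3.2.3).** The logistic model is to assess "baseline predictors such as disability level, anxiety, depression, sleep self-efficacy level, and intervention adherence". Baseline ISI is not in the list. The hypothesis is that higher disability, anxiety and depression, and lower self-efficacy and adherence, go with non-response.
- **Where the drop starts (section 2.5).** The ISI taken at screening also serves as the baseline ISI.
- **Entry range (section 2.3 and Table 1).** Entry requires "≥10 on Insomnia Severity Index", and "The range of scores on the ISI is 0–28, with ≥10 suggesting clinical insomnia". Admissible entry scores are therefore 10 to 28.
- **Predictors and sleep (section 2.5).** Disability, depression, anxiety and sleep self-efficacy are described as having a known two-way relationship with sleep and fatigue. Section 4.1 adds that depression and insomnia often occur together.
- **The other aims (sections 3.2.1 and 3.2.2).** Both contain the sentence "The analysis will be done adjusting for baseline as a covariate". Section 3.2.3 has no counterpart.

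**The concern.** Confounding by entry ISI needs two links. The first is from predictor to entry ISI, and the protocol itself asserts a relation of this kind for four of the five predictors. The second is from entry ISI to the size of the drop. The score that admits a participant is also the score from which change is measured, so measurement error in it produces regression to the mean: people who score high at screening tend to fall further. The rule also demands a larger relative improvement from mild cases (6/10 = 60% at entry 10) than from severe ones (6/28 = 21% at entry 28).

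If both links hold, participants with more depression, anxiety or disability enter with higher ISI and reach a 6-point drop more easily. Without entry ISI in the model, that pushes the odds ratio for response upward, against the stated hypothesis. The Introduction and the Discussion say that Aim 3 should help choose treatment for individuals, so a masked association or a wrong sign would matter even in an exploratory analysis.

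**Working it through.** **1. Planning figures.** The protocol gives no sample size, power or responder rate for Aim 3. The check borrows the ISI inputs of section 3.1: mean changes 13.8 (CBT-I) and 8.1 (control), SD 5.8, correlation 0.5 between follow-ups, two-sided 5%, 90% power. With variance factor (1 + 0.5)/2 = 0.75:

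n per arm = 2 × (1.960 + 1.282)² × 5.8² × 0.75 / 5.7² = 16.3, rounded up to 17.

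This is the protocol's figure, so the inputs are read as intended.

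**2. Expected responders.** With normal changes, P(drop ≥ 6) = 1 − Φ((6 − mean)/5.8).

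- CBT-I: 1 − Φ(−1.34) = 0.911
- Control: 1 − Φ(−0.36) = 0.641
- Of 35 + 35: 35 × (0.911 + 0.641) ≈ 54 responders and about 16 non-responders

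**3. A predictor with no effect beyond baseline.** The simulation used the changes and SD above. *Assumptions not in the documents:* entry ISI normal with SD 4, cut to 10–28; the drop grows by k points per extra entry point; the predictor correlates r with entry ISI. Six-week scores were limited to 0–28. The logistic models contained arm and one standardised predictor, with and without baseline ISI.

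Odds ratio for response per SD, entry mean 17:

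| k | r | without baseline ISI | with baseline ISI |
|---|---|---|---|
| 0 | 0.3 | 1.00 | 1.00 |
| 0 | 0.5 | 1.01 | 1.00 |
| 0.25 | 0.3 | 1.08 | 1.00 |
| 0.25 | 0.5 | 1.14 | 0.99 |
| 0.5 | 0.3 | 1.18 | 1.01 |
| 0.5 | 0.5 | 1.31 | 1.00 |

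Over entry means 16–20, k from 0.3 to 0.7 and r from 0.3 to 0.5, the range is 1.09–1.49 without baseline ISI and about 1.0 with it.

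**4. A predictor that truly worsens 6-week ISI by 1 point per SD.** Over the same ranges the odds ratio is about 0.82–1.10 without baseline ISI and about 0.71–0.74 with it. Most of the range is attenuation. Values above 1 appeared only at the corner with r = 0.5 and k = 0.7.

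**5. Precision at the real size.** For a standardised predictor, SE(log OR) ≈ 1/√(70 × 0.776 × 0.224) = 0.287. The 95% interval then extends by a factor of exp(1.96 × 0.287) ≈ 1.75 on either side.

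**The case against.** **The list is open.** Section 3.2.3 introduces the predictors with such as, and the full analysis plan is not shown. A reader might infer that baseline ISI is ruled out; the text does not say so. It is unnamed. What remains is that the article fixes the responder rule, names five predictors, and states baseline adjustment for Aims 1 and 2 but not for Aim 3.

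**The bias is not established.** A reader might infer that the predictors are confounded and that more depressed participants will look like better responders. The documents do not support that. They give no entry ISI distribution, no correlations and no slope, and the bias is nil when k = 0. Table 1 excludes severe depression and severe anxiety, which would tend to weaken the correlations. The floor offers little help to the stronger reading: someone entering at 10–13 cannot drop by 13.8, so change must depend on baseline somewhere, but this does not act at the 6-point threshold. Adherence is not a baseline trait, and section 2.5 does not include it among the variables related to sleep, so the point covers four predictors.

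**Noise is larger than the bias.** This is fair: a spurious odds ratio of 1.1–1.5 lies inside the factor of 1.75 from sampling error. But the bias has a predictable direction, opposite to the hypothesis, and does not shrink with more data.

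**Adjustment is debatable.** An unadjusted association is a legitimate predictive question, and entry ISI may partly lie on the path from depression or disability to outcome. That argues for showing both results, not for leaving the choice open.

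**Responders above the insomnia cut-off.** A drop of exactly 6 leaves the score at 10 or more from any entry score of 16 to 28, and section 2.3 describes the ISI "with ≥10 suggesting clinical insomnia". A reader might infer that the responder rule is wrong. It is not: it is labelled a minimal important difference, the aim concerns improvement, and nothing in the protocol requires responders to fall below 10.

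**Conclusion.** The concern holds as a risk, not as a demonstrated bias. Response is a change from the selecting score, four of the named predictors are said to be related to sleep, and entry ISI is not named in the one analysis where it matters most for interpretation. The estimate of about 1.1–1.5 per SD for a predictor without its own effect rests on assumed correlations of 0.3–0.5, k of 0.3–0.7, and entry means of 16–20 with SD 4. At k = 0.25 it is 1.14 or less, and at k = 0 it vanishes. Aim 3 is exploratory, and the primary ISI analysis already adjusts for baseline. The change is worth making because the value is already collected and the possible distortion runs against the stated hypothesis.

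**What to change.** In section 3.2.3, name baseline (screening) ISI as a covariate in the Aim 3 logistic models, in line with Aims 1 and 2. The unadjusted odds ratios can be shown beside the adjusted ones.

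**Cost.** One sentence, no new data, and one more parameter in a small model. With about 16 non-responders, the five named predictors leave 16/5 ≈ 3 non-responders per parameter; adding arm and baseline ISI leaves 16/7 ≈ 2. Predictors may therefore have to be entered one at a time, each with baseline ISI.

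**Optional.** The number of participants with ISI below 10 at 6 weeks could be reported descriptively beside the responder rate. This is an addition, not a correction, and the 6-point rule can stay.
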